### Surgical methods

Cervical approach, preparation, resection approach and vessel control are not limited per protocol in either group. The only binding preparation principles in either group are visualization, monitoring and protection of the recurrent laryngeal nerve, as well as the identification and protection of the parathyroid glands following the national guideline [7]. Neuromonitoring is performed and recorded before and after resection via the vagus nerve. If unforeseen multinodular changes, suspected malignancy, or frozen-section assured malignancy requires total thyroidectomy in the intervention group, or even additional lymphadenectomy in either group, the reason will be documented on the case report form. Required by the intention-to-treat principle, patients must be followed up in the group to which they are randomized.

### Definition of endpoints and outcome measures

#### Primary endpoint

The incidence of transient hypoparathyroidism is defined as the primary endpoint. Transient hypoparathyroidism is defined as an inadequate parathyroid function not exceeding six months after surgery [14]. Serum calcium (Ca) and parathyroid hormone (PTH) levels and substitution medication to achieve normocalcaemia are used to assess hypoparathyroidism. According to the best of our knowledge, there is no evidence- or consensus-based definition of postoperative hypoparathyroidism based on calcium and PTH cutoff levels. In line with most experts, we define postoperative hypoparathyroidism as calcium and PTH levels below the normal range (Ca ≤ 2.1 mmol/l, PTH < 11 ng/l). Postoperative hypoparathyroidism is considered to be symptomatic in the case of at least one of the following symptoms: carpo-pedal paresthesia, numbness or spasms, and anxiety. Application type, form and dosage of Ca and vitamin D substitution therapy to achieve normocalcaemia (Ca = 2.2 to 2.7 mmol/l) are registered. Postoperative hypoparathyroidism is defined transient if calcium and vitamin-D substitution therapy to achieve normocalcaemia are required for less than six months after surgery. The parameters are recorded before surgery, at the day of discharge, 6 weeks, 6 months and 12 months after surgery.

#### Secondary endpoints

Secondary endpoints comprise the incidences of permanent hypoparathyroidism, recurrent Graves’ disease, temporary and permanent recurrent laryngeal nerve palsy and reoperations due to bleeding, and the number of inadvertently removed parathyroid glands, as well as changes of endocrine orbitopathies and quality of life. Permanent hypoparythroidism is defined as persisting inadequate parathyroid function exceeding six months after surgery [15,16]. The incidence of recurrent Graves’ disease is assessed through laboratory thyroid function tests as thyroid stimulating hormone (TSH) < 0.34 U/l, free triiodinethyronine (fT3) > 6.5 pmol/l, thyroxine (fT4) > 21 pmol/l, and TRAK > 1.75 U/l, at 6 weeks, 6 months and 12 months after surgery, with respect to concomitant substitution or thyrostatic medications to achieve euthyrosis, determined by laboratory thyroid function tests (TSH, fT3, fT4). Cervical ultrasound follows detection of elevated antibody levels to screen for recurrence. Reoperations are reported as serious adverse events. Incidences of temporary and permanent recurrent laryngeal nerve palsies are assessed through laryngoscopy on the day of discharge and in the case of pathological findings 6 weeks, 6 months and 12 months after surgery. The number of inadvertently removed parathyroid glands will be counted from histopathology reports at the day of discharge. Changes in endocrine orbitopathy are measured using the validated clinical eyelid, exophthalmos eye muscle, optic nerve (LEMO) score [17] before and 12 months after surgery. Changes in quality of life are scored before surgery and 6 weeks thereafter using the validated multipurpose questionnaire, the clinical studies 36-item medical outcomes study short-form general health survey (SF36) [18].

### Randomization, allocation concealment and blinding

A central randomization will be performed, stratified by the performing surgeons. Only surgeons who have performed at least 100 thyroidectomies working at a volume center accounting for more than 100 thyroidectomies per year will participate. A random sequence will be generated through computerized random assignment and concealed allocation. Patients and the observer are blinded to the applied surgical intervention. Intraoperative randomization will be performed. The surgeon will be unblinded after the skin incision, and the patient and the observer will be blinded throughout the whole study period. All assessments will be performed by personnel who are blinded to the study arms for the minimization of measurement bias. Data storage and analyses will be performed externally.

### Sample size

The trial is designed on the basis of a critical appraisal of current evidence. According to the only existing randomized controlled trial by Witte *et al*. [1], a significant reduction in the incidence of transient hypoparathyroidism from 28% in the total thyroidectomy group to 12% in the near-total thyroidectomy group is suspected. Using a level of significance of 5% and a power of 80%, 97 patients per group are needed to detect the pre-specific difference when applying a chi square test (2-sided) without Yates's correction for continuity. With a dropout rate of 5% between obtaining informed consent and randomization, a total sample of 206 patients need to be recruited to the trial. Analysis of the primary endpoint will be performed by an adjusted logistic regression model. Therefore, it is to be expected that including covariates of prognostic importance in the logistic regression model will increase the power as compared to the chi square test. However, since the impact of the covariates cannot be determined a priori, a potentially liberal sample size estimation for the chi square test seems appropriate.

### Analysis

The primary hypothesis is whether the rate of transient hypoparathyroidism within 6 months after surgery is lower in patients after near-total compared to total thyroidectomy. A binary logistic regression model will be applied for the intervention comparison of the rates, adjusting for age, gender, hyperthyrosis and endocrine orbitopathy as additive covariates. The dropout rate can be assumed to be small, and therefore, few missing values are expected with respect to the primary endpoint. If missing values occur their reason of omission will be explored. Depending on the properties and magnitude of missing values, an appropriate estimation will be specified before the analysis of the primary endpoint. Concerning other secondary endpoints, exploratory data analysis will be performed calculating appropriate summary measures for the empirical distribution as well as calculation of descriptive two-sided 95% confidence intervals and *P*-values. Sensitivity analyses will be conducted for the per-protocol population as well as for appropriate subgroups. The safety analysis includes calculation and comparison of frequencies and rates of adverse and serious adverse events. Furthermore, statistical methods are used to assess the quality of data and the homogeneity of intervention groups.

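### Randomisation is stratified by surgeon but the primary model leaves surgeon out; if surgeons differ in risk, the test is conservative and gives up a few points of power

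*Protocol article*

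**What the plan says.** On design, the section on randomization, allocation concealment and blinding states: "A central randomization will be performed, stratified by the performing surgeons". No other stratification factor is named.

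On analysis, the Analysis section fixes a binary logistic model for the primary comparison and describes it as "adjusting for age, gender, hyperthyrosis and endocrine orbitopathy as additive covariates". Surgeon is not in that list, and no stratified, conditional or random-effect term for surgeon appears anywhere in the article.

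The Sample size section assumes a fall "from 28% in the total thyroidectomy group to 12% in the near-total thyroidectomy group is suspected". The number comes out as follows: "Using a level of significance of 5% and a power of 80%, 97 patients per group are needed". The test behind it is an uncorrected two-sided chi-square. The section then takes the view that, in the adjusted analysis, "including covariates of prognostic importance in the logistic regression model will increase the power as compared to the chi square test".

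**The concern.** Stratifying by surgeon balances the arms within each surgeon, so differences between surgeons largely drop out of the treatment comparison. A model without surgeon still counts those differences as random error. Its standard error is then too large for the design, the test runs below its nominal 5% level, and power that the stratification could have supplied goes unused.

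This matters only if surgeons differ in risk. The article makes that plausible: the Abstract calls preparation technique influential, and the Surgical methods section leaves approach, preparation and vessel control open apart from rules on protecting the nerve and the parathyroid glands. The Sample size section also counts on prognostic covariates for extra power, while the one factor chosen for balancing is absent from the model.

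**Working it through.** **1. The plan's own figure.** Inputs from the Sample size section: p0 = 0.28, p1 = 0.12, two-sided 5%, power 80%, no continuity correction. The mean rate is 0.20.

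n = [1.960·√(2·0.20·0.80) + 0.842·√(0.28·0.72 + 0.12·0.88)]² / 0.16² = (1.109 + 0.466)² / 0.0256 ≈ 96.9, so 97 per group. With 5% loss, 97/0.95 = 102.1, so 103 per group and 206 in total. Both stated figures reproduce.

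**2. Direction, by formula.** Suppose there is no treatment effect, a mean risk p = 0.20, and surgeon-specific risks with variance V. With full balance within surgeon, the true variance of the risk difference is f = 1 − V/[p(1−p)] times the variance that the unadjusted test uses. The actual level is 2Φ(−1.96/√f). V comes from numerical integration of a normal surgeon effect on the logit scale, with the mean risk held at 0.20.

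| Logit SD (assumed) | SD of surgeon risks | f | Actual level |
|---|---|---|---|
| 0.5 | 0.078 | 0.962 | 4.6% |
| 0.8 | 0.121 | 0.908 | 4.0% |
| 1.2 | 0.169 | 0.822 | 3.1% |

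**3. Size, by simulation.** The runs used 194 patients, 20 surgeons, permuted blocks of 4 within surgeon, rates of 20%/20% (null) or 28%/12% (alternative), and 8,000 runs per cell. Surgeon number, block size and SD are assumptions. The number 20 is borrowed from the count of centres in the Trial status section. The four named covariates were not simulated. CMH is the Cochran-Mantel-Haenszel test stratified by surgeon.

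| Logit SD | Type I: Wald, no surgeon | Type I: chi-square, no surgeon | Type I: CMH | Power: Wald, no surgeon | Power: chi-square, no surgeon | Power: CMH |
|---|---|---|---|---|---|---|
| 0 | 4.5% | 4.8% | 4.8% | 79.7% | 80.5% | 80.1% |
| 0.5 | 4.5% | 4.9% | 5.2% | 81.1% | 81.9% | 82.4% |
| 0.8 | 3.9% | 4.1% | 5.0% | 80.7% | 81.6% | 83.8% |
| 1.2 | 3.1% | 3.3% | 4.7% | 81.7% | 82.6% | 86.3% |

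Simulation error (one standard error) is about √(0.05·0.95/8000) = 0.24 points for the level and √(0.8·0.2/8000) = 0.45 points for power. The Wald test is slightly conservative even with no surgeon effect, so chi-square against CMH is the fairer pairing. It gives about 0, 0.5, 2 and 4 points across the four rows; Wald against CMH gives 0.4, 1.3, 3.1 and 4.6.

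**4. The remedy itself.** Likelihood-ratio tests with and without a random surgeon intercept were compared in the same runs (20 surgeons; 1,000 runs at SD 0, otherwise 1,500). Power without and with the intercept was:
- SD 0: 81.8% and 82.2% (gain 0.4)
- SD 0.5: 80.0% and 81.0% (gain 1.0)
- SD 0.8: 81.9% and 83.7% (gain 1.8)
- SD 1.2: 82.1% and 86.5% (gain 4.4)

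Type I error with the intercept was 5.5%, 5.3%, 5.9% and 5.1%, where one standard error is about 0.6 to 0.7 points. One fixed effect per surgeon gave 6.3%, 6.1%, 6.1% and 5.1%, slightly liberal.

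**5. More surgeons.** At 40 surgeons (194/40 ≈ 5 patients each), Wald type I error without surgeon was 4.0% and 3.1% at SD 0.8 and 1.2. Power was 80.9% against 82.3% (CMH) and 82.0% against 85.5%. With no surgeon effect, CMH lost power: 78.6% against 80.2%. At 60 surgeons (about 3 patients each) the loss with no surgeon effect is larger, about 4 points; a run with uneven surgeon loads gave 74.8% against 80.5%. Full stratification discards surgeons whose patients all had the same outcome or all fell in one arm.

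**The case against.** Several arguments against the point have force.

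- **Surgeon may matter little.** The Background names extent of resection as the leading element of technique, and that is what is randomised. Entry is limited to experienced surgeons at high-volume centres, and nerve and parathyroid protection is binding on all. A reader might infer that the article makes technique a main cause and surgeon strongly prognostic; it does not. Only plausibility stands, so the point must stay conditional.
- **Nothing promised fails.** Power without surgeon stays near 80% in every scenario. The expected gain from prognostic covariates could still come from the four that are named, so the Sample size section is not contradicted.
- **Intervals would not narrow.** A reader might expect tighter confidence intervals after adjustment. The odds ratio is non-collapsible: conditioning on surgeon changes the quantity estimated and raises its standard error. At 20 surgeons and SD 0.8, the median standard error of the log odds ratio was 0.390 unadjusted and 0.418 surgeon-stratified. The gain lies in the test.
- **An unseen analysis plan may deal with surgeon.** It may, but the article gives a specific covariate list for the primary model. Adding surgeon later would depart from what is published, so the mismatch is in this document.

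**Conclusion.** The point holds as a conditional matter of efficiency and calibration. The design balances on surgeon and the stated primary model ignores it. If surgeons differ in risk, the test is conservative and weaker than a surgeon-adjusted one: roughly 2 to 3 points of power at a logit SD of 0.8 and 4 to 5 points at 1.2, with 20 surgeons. At 0.5 or below the loss is about 1 point or none. These sizes depend on a surgeon number and a between-surgeon SD that the article does not give, and on simulations without the four named covariates.

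A reader might infer that the omission invalidates the trial, produces false positives or leaves it underpowered. The figures show the opposite: the error rate falls below 5%, and the planned power is kept.

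**What to change.** In the Analysis section, add performing surgeon to the primary logistic model as a random intercept, keep age, gender, hyperthyrosis and endocrine orbitopathy, and state in advance that centre replaces surgeon if the model does not converge. Settle this before the primary endpoint is analysed.

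Do not enter one fixed effect per surgeon. Do not treat conditional logistic regression or a fully surgeon-stratified test as interchangeable with the random intercept: with 40 to 60 surgeons and few patients each, full stratification can cost about 2 to 4 points of power when surgeons do not differ. The random intercept should avoid most of that loss, but it was simulated only at 20 surgeons.

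The cost is a sentence or two. Surgeon is already known from randomisation, so no new data are needed. The model becomes slightly more complex, and the reported odds ratio becomes conditional on surgeon, which the text should say.

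### The primary logistic model does not adjust for preoperative calcium and PTH, which the trial records and whose postoperative values help define the event; a modest gain in efficiency may be forgone

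*Protocol article*

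**What the plan says.** The Primary endpoint section defines postoperative hypoparathyroidism as "calcium and PTH levels below the normal range (Ca ≤ 2.1 mmol/l, PTH < 11 ng/l". It also uses substitution therapy: the condition counts as transient if calcium and vitamin D are needed for less than six months. On timing it states: "The parameters are recorded before surgery, at the day of discharge, 6 weeks, 6 months and 12 months after surgery". A preoperative calcium and PTH value is therefore planned for every patient.

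The Analysis section names the primary model, a binary logistic regression "adjusting for age, gender, hyperthyrosis and endocrine orbitopathy as additive covariates". The list is explicit, and baseline calcium and PTH are not on it.

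The Sample size section gives the reason for adjusting. It expects that "including covariates of prognostic importance in the logistic regression model will increase the power as compared to the chi square test". It adds that the size of this effect cannot be known in advance, and it therefore sizes the trial on the chi-square test.

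**The concern.** When an outcome is defined by a measurement crossing a fixed limit, the preoperative value of that measurement is the natural first candidate for adjustment. A patient who starts near the limit needs a smaller fall to become an event. The article argues for adjustment on grounds of power, yet its list omits the two baseline variables closest to the outcome and gives no reason why the four chosen ones should predict better. At stake is some power, and some protection of the primary comparison when the arms happen to differ in preoperative calcium or PTH. The data are collected anyway.

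**Working it through.** **1. The plan's own figure.** Inputs from Sample size: event rates "from 28% in the total thyroidectomy group to 12% in the near-total thyroidectomy group is suspected"; two-sided alpha 0.05; target power 0.80; chi-square comparison with no continuity correction; equal arms. The mean rate is (0.28 + 0.12)/2 = 0.20.

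n = [1.960 × √(2 × 0.20 × 0.80) + 0.842 × √(0.28 × 0.72 + 0.12 × 0.88)]² / (0.28 − 0.12)²
= [1.960 × 0.5657 + 0.842 × 0.5543]² / 0.0256 = 96.9, so 97 per group.

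Power at 97 per group is 0.800. With 5% dropout, 97/0.95 = 102.1, so 103 per group and 206 in total. Both figures reproduce, and no covariate enters either of them.

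**2. Events available.** 97 × 0.28 + 97 × 0.12 = 38.8. Treatment plus four covariates, each counted as one parameter, gives 38.8/5 = 7.8 events per parameter. Adding calcium and PTH gives 38.8/7 = 5.5.

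**3. Effect of adding the two baselines.** Trials were simulated with 97 per arm and marginal rates held at 28% and 12%, using a likelihood-ratio test for treatment. The model with treatment and four covariates was compared with the same model plus two more. Assumptions: the four listed covariates carry no prognostic information, and calcium and PTH are independent. Their prognostic strength is assumed over a range, because the documents give none.

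| Odds ratio per SD, each | Run A power, 4 covariates → plus 2 | Run A change | Run B change |
|---|---|---|---|
| 1.0 | 81.0% → 80.9% | −0.1 | −0.5 |
| 1.3 | 80.7% → 82.1% | +1.4 | +1.1 |
| 1.5 | 81.5% → 82.6% | +1.1 | +1.6 |
| 1.75 | 81.2% → 84.5% | +3.3 | +3.1 |
| 2.0 | 82.0% → 86.1% | +4.1 | +3.7 |

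Run A used 4,000 trials per setting.

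A third run (6,000 trials per setting) expressed strength per SD of the combined score (calcium + PTH)/√2. An odds ratio of exp(g) on that scale equals exp(g/√2) for each covariate.
- Combined 1.65 (each about 1.42): 80.2% → 81.5%, +1.3 points.
- Combined 2.12 (each about 1.70): 80.3% → 82.6%, +2.3 points.
- Combined 2.72 (each about 2.03): 80.9% → 85.8%, +4.9 points.
- Combined 4.48 (each about 2.89): 81.1% → 89.6%, +8.5 points.

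The three runs broadly agree. The largest gains need an association that nothing in the article supports.

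**4. Type I error.** In run A it was 5.1–6.0% with the two extra terms and 4.9–5.6% without (simulation error about 0.35 points). In run B it was 4.9–5.6% with and 4.9–5.8% without.

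**The case against.** The strongest case on the other side is that the article prespecifies a valid adjusted model, and that the choice of covariates is a matter of judgement.

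- **No planned power is lost.** This stands. The 80% comes from the unadjusted test (step 1), so any gain from covariates is a surplus.
- **The prognostic strength is unknown and may be low.** This stands. Background points to preparation technique and extent of resection, not to preoperative chemistry. Excluding coincident hyperparathyroidism and earlier thyroid or parathyroid surgery narrows the baseline range. The endpoint also depends on substitution therapy and its duration, so baseline values predict it less directly than a pure threshold would imply.
- **The simulations treat the listed covariates as non-prognostic.** This stands as a limit. If the four are prognostic or correlated with calcium or PTH, the added gain would differ.
- **Too few events for two more terms.** This mostly fails. With two pure-noise covariates power changes by −0.1 to −0.5 points, and type I error stays near 5%. A larger re-run (20,000 null and 12,000 alternative trials per setting) put the type I excess of the longer model at 0.1–0.3 points. After type I error was equalised, it still gave changes of −0.2, +0.6, +1.6 and +3.1 points at odds ratios of 1.0, 1.3, 1.5 and 1.75.
- **Chance imbalance is already covered by the test.** This stands as a statement about validity. With 97 per arm the SD of a standardised baseline difference is √(2/97) = 0.144, so a difference above 0.2 SD in either direction occurs in about 16% of trials. Adjustment helps in the unlucky ones, but their cost is already averaged into the overall power.

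**Conclusion.** The point holds as a missed opportunity for efficiency, not as an error. The primary model omits two recorded baseline measurements whose postoperative values help define the event. The power forgone is about 0 to 2 points for weak to moderate prognostic strength (odds ratio up to about 1.5 per SD each) and about 3 to 4 points at 1.75 to 2.0, under the simulation assumptions stated above.

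Three stronger readings are tempting, and the documents support none of them.
- A reader might infer that power is certainly given up. That needs an association the article does not report; with none, there is no gain.
- A reader might infer that the stated 80% depends on covariates, or that the gain the article hopes for goes largely unused. The sample size takes no covariate credit, and the second claim would require showing that the four listed covariates are not prognostic.
- A reader might infer that chance imbalance in calcium or PTH biases the comparison. Under randomisation it does not; it adds variability that the test already allows for.

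The analysis plan is not shown. The point concerns the covariate list that the article itself fixes.

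**What to change.** Before unblinding, amend the Analysis section so that the primary logistic model also includes preoperative serum calcium and log-transformed preoperative PTH, each as one continuous linear term. State that treatment is tested by likelihood ratio. Report the model with the four listed covariates as a sensitivity analysis.

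The cost is about one sentence and no new data; Trial status shows funding still awaited, so the change can be made early. The downsides are small: two more coefficients (about 5.5 rather than 7.8 events per parameter) and a simple, prespecified imputation where a preoperative value is missing. If a shorter model is preferred, calcium and PTH could replace weaker covariates, or a penalised fit could be used.

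The plan should also note that the two models' odds ratios need not agree even with perfectly balanced arms. With the marginal rates fixed, the simulated conditional odds ratio moves from 0.351 with no baseline association to 0.300 at an odds ratio of 2.72 per SD of the combined score. Such a difference would not by itself signal a problem.
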